## Methods and Materials

### Study Design and Setting

The J-MIND-Diabetes study was designed as a 18-month, open-labeled, randomized, controlled, multicenter trial of multi-domain intervention targeting modifiable risk factors for dementia among T2DM patients with cognitive impairment. To be organized by a central coordinating center at the National Center for Geriatrics and Gerontology (NCGG), this study involves 16 centers located in Japan. This study will randomize 300 T2DM patients with cognitive impairment into intervention or control groups. The multi-domain intervention will address the following 4 domains: (1) management of metabolic and vascular risk factors (diabetes, hypertension, and dyslipidemia); (2) physical exercise and self-monitoring of physical activity; (3) nutritional guidance; and (4) promoting social participation. The control group will receive usual diabetes care and general instructions on dementia prevention. The primary and secondary outcomes will be assessed at baseline, 6, and 18 months in both groups (see the study flow diagram shown in Figure 1).

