#### Primary Outcome: Cognitive Change at 18-Month Follow-Up (Composite Score)

The primary outcome is change from baseline at 18 months in a global composite score using several neuropsychological tests (Table 2), which include tests of global cognitive function [MoCA-J (27), MMSE (Folstein et al., 1975)]; memory [ROCFT (Strauss et al., 2006), delayed recall test of a 10-word list derived from the Alzheimer's Disease Assessment Scale-cognitive subscale (ADAS-Cog) (Mohs and Cohen, 1988)]; attention [Wechsler Adult Intelligence Scale (WAIS) Digit Span (Wechsler, 1997)]; executive function/processing speed [Trail Making Test (TMT) (Lezak, 2004), Digit Symbol Substitution Test (DSST) (Wechsler, 1997), Letter word fluency test (Lezak, 2004)]. The composite score will be generated by averaging the Z scores of each neuropsychological test standardized with baseline means and standard deviations (SDs) for each test from the intention-to-treat population. A Z score of −1, for example, represents a score that is 1 SD below the baseline mean. A one-point decrease on the composite score indicates an average decline of 1 SD across the neuropsychological tests.

**Table 2 T2:** Primary outcome measures in the J-MIND-Diabetes trial.

**Domain**	**Neuropsychological test**
Global cognitive function	• Japanese version of the montreal cognitive assessment (Fujiwara et al., 2010) • Mini-mental state examination (Folstein et al., 1975)
Memory	• Rey-osterrieth complex figure test (Strauss et al., 2006) • Word-list memory [ADAS-cog (Mohs and Cohen, 1988)]
Working memory	• Digit span test [WAIS-III (Wechsler, 1997)]
Processing speed	• Digit symbol substitution test [WAIS-III (Wechsler, 1997)]
Attention	• Trail making test part A (Lezak, 2004)
Executive function	• Trail making test part B (Lezak, 2004) • Letter word fluency test (Lezak, 2004)

*ADAS-cog, alzheimer's disease assessment scale-cognitive subscale; J-MIND-Diabetes, japan-multi-domain intervention trial for prevention of dementia in older adults with diabetes; WAIS, wechsler adult intelligence scale*.

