### Statistical Considerations

#### Sample Size

Using the open source sample size calculator (http://www.openepi.com/SampleSize/SSMean.htm), the sample size was calculated based on preliminary data from MMSE assessments over 1-year (1.03 ± 0.36 years) in 83 patients with MCI and T2DM classified into category II among the Memory Clinic at the NCGG, since no multi-domain intervention trials have been conducted to date in this population. The mean change in MMSE score among 83 patients was −1.45 ± 3.55. Of these, the optimally controlled group (n = 30) showed a mean change in MMSE score of −0.33 ± 2.58. Based on these preliminary data, it was hypothesized that the present study is likely to detect differences in change of cognitive function between the intervention and control groups (intervention group vs. control group, −0.33 ± 2.58 vs. −1.45 ± 3.55). With a two-sided significance level of 5% and a statistical power of 80%, the total sample size required for the unpaired *t*-test was calculated as 242. In addition, dropout rates at final follow-up is estimated to be 15–20% at each institution, thus a total of 300 patients are required.

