#### Randomization and Blinding

In this open-label intervention study, participants will be centrally randomized at a 1:1 allocation ratio into intervention and control groups using the stratified permuted-block randomization methods based on the following stratification variables:

Institutions (1–15 institutions).Age at enrollment (70–77 years vs. 78–85 years).Glycemic control relative to the glycemic targets recommended by the JDS/JGS joint committee (optimally controlled vs. poorly or excessively controlled).Drugs potentially associated with severe hypoglycemia such as insulin, sulfonylureas and glinides (those receiving these drugs vs. those not receiving these drugs).

The randomization sequences will be generated by a trial statistician ([name]) by using Proc Plan in SAS version 9.4 (SAS Institute, Cary, NC, USA). Study participants and research staff including investigators and clinicians at each institution will be unaware of the randomization sequences and block size. Research staff responsible for primary outcome data collection will also be blinded to group assignment, to which, however, the intervening research staff and the participants will be not blinded.

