#### Data Analyses

Data will be presented as means, medians, standard deviations, ranges and interquartile ranges for continuous and ordinal variables, and counts and percentages for categorical variables. Differences in baseline clinical characteristics between the intervention and control groups will be examined for significance by using the *t*-test or the Mann-Whitney U test for continuous variables and by the chi-squared test or the Fisher's exact test for categorical variables, as appropriate.

To evaluate differences in cognitive changes from baseline at 18-month follow-up between the intervention and control groups, the mixed-effects model for repeated measures (MMRM) with an unstructured covariance structure will be conducted using groups, time of the visit, group by time interaction, and baseline composite cognitive score as covariates. For the secondary continuous variables, the same analyses using MMRM will be performed. For the secondary categorical variables, logistic regression analyses or chi-squared tests will be conducted as appropriate. Frequencies of adverse events and serious adverse events will be summarized and compared between the intervention and control groups by using the chi-squared test or the Fisher's exact test.

All statistical analyses will be performed using SAS 9.4 (SAS Institute, Cary, NC, USA). *P*-values <0.05 will be considered statistically significant.

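### The primary MMRM gives baseline cognition one common slope at 6 and 18 months; a baseline-by-visit term would protect the 18-month contrast at almost no cost

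*Protocol article*

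**What the plan says.** The Primary Outcome section sets a single time point: "The primary outcome is change from baseline at 18 months in a global composite score". Study Design and Setting gives the schedule: "The primary and secondary outcomes will be assessed at baseline, 6, and 18 months in both groups". There are therefore two post-baseline visits.

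Data Analyses fixes the primary model as a "mixed-effects model for repeated measures (MMRM) with an unstructured covariance structure", fitted "using groups, time of the visit, group by time interaction, and baseline composite cognitive score as covariates". One interaction with time is named (group by time). An interaction of baseline with time is not. The same MMRM is to be used for the secondary continuous outcomes.

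Sample Size adds that "dropout rates at final follow-up is estimated to be 15–20% at each institution". Nothing is said about whether dropout is related to baseline cognition or to arm.

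**The concern.** The unstructured covariance leaves the relation between the two follow-up visits free. The single baseline slope then restricts how each visit relates to baseline, and the article gives no ground for that restriction. The second follow-up interval is 12 months and the first is 6, so equal slopes cannot be taken for granted.

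If the slopes differ, the common slope is a weighted compromise. Where residual variance is smaller at 6 months, it is drawn toward the 6-month value, and the misfit falls mainly on the primary visit. Two things are then at stake:

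- **Precision.** Baseline adjustment removes less variance at 18 months than it could.
- **Bias.** If dropout depends on baseline cognition and does so differently by arm, a misfitted slope no longer removes that dependence, although baseline is in the model.

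**Working it through.** **The plan's own figure.** Inputs from Sample Size: "intervention group vs. control group, −0.33 ± 2.58 vs. −1.45 ± 3.55", two-sided 5%, power 80%. Per arm: (2.58² + 3.55²)(1.960 + 0.842)² / 1.12² = 120.5, rounded up to 121, total 242 as stated. Dividing by 0.85 and 0.80 gives 285 and 303, so 300 is in line. This is an unadjusted t-test on MMSE change, so no planned figure depends on the baseline term.

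**When slopes differ.** The slope of change on baseline at a visit is ρ × (SD at visit / SD at baseline) − 1. A falling correlation does not by itself make slopes unequal: ρ of 0.90 with SD ratio 1.00, and ρ of 0.80 with SD ratio 1.125, both give −0.10.

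**Assumed inputs.** Baseline SD is set to 1. Correlations are listed as baseline–6, baseline–18 and 6–18 months. All are assumptions, because the article gives none for the composite.

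| Case | Correlations | SD at 6 / 18 | True slopes 6 / 18 |
|---|---|---|---|
| 1 | 0.85, 0.75, 0.85 | 1 / 1.1 | −0.15 / −0.175 |
| 2 | 0.85, 0.65, 0.75 | 1 / 1 | −0.15 / −0.35 |
| 3 | 0.85, 0.85, 0.90 | 1 / 1.3 | −0.15 / +0.105 |
| 4 | 0.90, 0.50, 0.60 | 1 / 1 | −0.10 / −0.50 |

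**Fitted common slope, no dropout.** Let v6, v18 and c be the residual variances and covariance given baseline. The weight on the 18-month slope is (v6 − c) / (v6 + v18 − 2c). In case 2, v6 = 1 − 0.85² = 0.2775, v18 = 1 − 0.65² = 0.5775 and c = 0.75 − 0.85 × 0.65 = 0.1975. The weight is 0.08 / 0.46 = 0.174 and the common slope is −0.15 − 0.174 × 0.20 = −0.185. A fit to 1,000,000 simulated patients gave the same value.

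**Precision, no dropout.** The variance of the 18-month contrast rises by (slope error)² / v18. Case 2: (0.35 − 0.185)² / 0.5775 = 4.7%. The simulated fits gave 0.1%, 4.7%, 9.6% and 18.8% for cases 1 to 4, expressed as extra sample size. The contrast was unbiased in every case.

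**Bias with 20% dropout.** Bias is the difference between the common-slope and visit-specific estimates, in absolute value. Dropout has odds ratio 2 per baseline SD, either in the intervention arm only or in opposite directions in the two arms. The standard error is that at N = 300. The planned standardised effect is 1.12 / 3.10 = 0.361 SD of change. The SD of 18-month change is √(1 + k² − 2ρk), with k the SD at 18 months: 0.748, 0.837, 0.693 and 1.000.

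| Case | One arm: bias | In SE | Share of planned effect | Opposite: bias | In SE |
|---|---|---|---|---|---|
| 1 | 0.0032 | 0.04 | 1.2% | 0.0065 | 0.07 |
| 2 | 0.0257 | 0.26 | 8.5% | 0.0506 | 0.52 |
| 3 | 0.0321 | 0.36 | 12.8% | 0.0638 | 0.71 |
| 4 | 0.0503 | 0.42 | 13.9% | 0.1025 | 0.85 |

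For example, case 2 with one arm: 0.0257 / (0.361 × 0.837) = 8.5%. With the same dependence in both arms the two models differed by at most 0.001. With visit-specific slopes there was no bias beyond simulation error.

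**Error rates.** In 1,500 simulated null trials of 300 patients with one-arm dependence, type I error was 0.042 to 0.068 with the common slope and 0.041 to 0.062 with visit-specific slopes (simulation error about 0.006).

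**A second set of assumptions.** Here the true effect was 0.15, baseline SD 0.65, slopes −0.10 / −0.30, and dropout about 18%. One-arm dependence (log-odds −0.5 to −0.8 per SD) gave bias of −0.012 to −0.019, which is 8 to 13% of the effect, and power of 0.62 to 0.68 against 0.77 with the interaction. With slopes −0.10 / −0.20 and unequal dependence in both arms (log-odds −0.8 and −0.5), bias was −0.003 (2%) and power 0.75 against 0.77. With slopes −0.05 / −0.08 the two models agreed (standard errors 0.0547 and 0.0550, within simulation error).

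**The case against.** The strongest reply is that nothing in the article shows unequal slopes. A baseline main effect is a common MMRM specification, and if scores spread out over time while correlations fall, the slopes may be close. This stands. A reader might infer that the model certainly uses the wrong slope and wastes precision. The article neither shows that nor rules it out.

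Bias needs three conditions together: unequal slopes, dropout related to baseline cognition, and a relation that differs by arm. Only the intervention arm has exercise sessions at least twice a month and daily records, which makes differential dropout conceivable in cognitively impaired patients. But outcome visits are the same in both arms, and leaving the programme is not the same as missing the 18-month assessment. This also stands. A reader might seize on larger biases, such as 0.85 standard errors above, or 24% of the effect (about 0.036 of 0.15) under the second set of assumptions. Both need opposite dependence in the two arms, which nothing in the article suggests.

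Finally, the article condenses a fuller protocol, and an SAP not shown could add the term. That limits confidence but does not dispose of the point: the article lists the model terms explicitly, and includes one interaction with time without the other.

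**Conclusion.** The point holds as a minor specification weakness in a model that is stated, not left open. The loss is about 0% of sample size if the two slopes nearly match, and 5 to 19% in the three unequal-slope cases. Without dropout, or with the same baseline dependence in both arms, the 18-month contrast is not biased. With one-arm dependence and 20% dropout the bias stays below half a standard error; it can still cost some power when the slopes differ markedly. Type I error is little changed, and the 242 and 300 are unaffected.

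All magnitudes rest on assumed composite variances, correlations and dropout patterns. The claim that the 18-month visit carries most of the misfit also assumes that residual variance is smaller at 6 months than at 18. What does not depend on these assumptions is the asymmetry: the added term costs almost nothing if it is not needed, and removes an avoidable restriction if it is.

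**What to change.** In Data Analyses, add the baseline composite by visit interaction to the listed terms of the primary MMRM, and state that the group contrast at 18 months remains the primary estimate. In the secondary MMRMs, use the corresponding baseline by visit term wherever an outcome is measured at both 6 and 18 months. Outcomes measured only at baseline and 18 months, such as the continuous glucose monitoring indices and the food frequency questionnaire, have one follow-up visit and do not need it.

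The cost is one degree of freedom per model with two post-baseline visits, and one phrase of text. No data, visits or sample size change. The term should be fixed before unblinded data are seen, so that it is not a post hoc choice. If the SAP already contains it, the two documents need only be aligned.

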#### Assessment

All subjects will complete neuropsychological tests, comprehensive geriatric assessments (CGA), and blood and urinary tests at baseline, as well as at 6- and 18-month follow-up. Additionally, brain MRI or CT will be performed by the scanner available at each institution at baseline and 18-month follow-up to detect any local lesion such as cerebral infarctions that can greatly affect cognitive function. Adherence to the intervention programs and adverse events will be also monitored during this trial. The timeline for scheduled assessments following the SPIRIT guidelines is shown in Figure 2.

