##### Improvement in Outcomes Related to T2DM

Metabolic control: In blood tests performed at baseline and 6-/18-month follow-up, the participants will be assessed for glycated hemoglobin (HbA1c), glycoalbumin, fasting blood glucose levels, and fasting blood insulin levels. Additionally, at baseline and 18-month follow-up, they will also be evaluated for SD of blood glucose levels, mean amplitude of glycemic excursions (MAGE), continuous overall net glycemic action (CONGA), and mean of daily differences (MODD) (Inchiostro et al., 2013) by using the FreeStyle Libre Pro system (Abbott Diabetes Care, Tokyo, Japan), a continuous glucose monitoring (CGM) system capable of providing records of glucose levels, trends, and patterns in each individual for up to 14 days. Moreover, the averaged percentage of time each participant spent in hypoglycemia (<70 mg/dL) will be also calculated.Self-reported hypoglycemic events: Participants will be assessed for hypoglycemic events by asking the following questions: “Did you experience any hypoglycemia episode that required the assistance of another person in the past year?” (Yes/No); “Did you experience any symptoms, such as sweating, palpitation, or trembling, in the past year?” (Yes/No); and “Did you experience any symptoms, such as lightheadedness, unsteadiness, dizziness, or visual disturbance, in the past year?”Microangiopathy and macroangiopathy: Participants will be assessed at baseline and at follow-up for microangiopathy including retinopathy, nephropathy, and neuropathy. Participants will be assessed for retinopathy categorized into five stages (Wilkinson et al., 2003): (1) no apparent retinopathy, (2) mild non-proliferative retinopathy, (3) moderate non-proliferative retinopathy, (4) severe non-proliferative retinopathy, (5) proliferative diabetic retinopathy. They will also be assessed for presence or absence of edema in the macula of the retina as well as for visual acuity by the Landolt Ring Test. Participants will be assessed for diabetic nephropathy categorized into five stages based on urinary albumin (mg/gCr), urinary protein (g/gCr), or estimated glomerular filtration rate (eGFR, mL/min/1.73m2) (Japan Diabetes Society, 2016): (1) Pre-nephropathy, (2) incipient nephropathy, (3) overt nephropathy, (4) kidney failure, (5) dialysis therapy. They will also be assessed for diabetic neuropathy using the Achilles tendon reflex test and vibration testing with a 128-Hz graduated tuning fork. Again, they will also be assessed for macroangiopathy, including ischemic heart disease, stroke, and peripheral vascular disease, based on their clinical charts and MR or CT imaging (Japan Diabetes Society, 2016).

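### Read literally, the secondary analyses adjust for baseline cognition, not each outcome's own baseline, and permit an unordered chi-squared test for five-stage outcomes

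*Protocol article*

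**What the plan says.** All of the analysis text is in the Data Analyses section of the protocol article. The MMRM for cognitive change contains group, visit, "group by time interaction, and baseline composite cognitive score as covariates". No other baseline covariate is named. Two sentences then cover the secondary outcomes:

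- Continuous: "For the secondary continuous variables, the same analyses using MMRM will be performed".
- Categorical: "For the secondary categorical variables, logistic regression analyses or chi-squared tests will be conducted as appropriate".

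The baseline values are available. The Assessment section says: "All subjects will complete neuropsychological tests, comprehensive geriatric assessments (CGA), and blood and urinary tests at baseline, as well as at 6- and 18-month follow-up". For the complications, the section on outcomes related to T2DM says: "Participants will be assessed at baseline and at follow-up for microangiopathy including retinopathy, nephropathy, and neuropathy".

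Two of those complications are ordered scales: "Participants will be assessed for retinopathy categorized into five stages", and "Participants will be assessed for diabetic nephropathy categorized into five stages". Some continuous outcomes have a single follow-up measurement. For the glucose-variability measures from continuous glucose monitoring (CGM): "Additionally, at baseline and 18-month follow-up, they will also be evaluated for SD of blood glucose levels". The food frequency questionnaire is likewise scheduled at baseline and 18 months only.

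**The concern.** For the primary outcome, the composite score at baseline is the outcome's own baseline, so the model is sound. If the same model is carried over unchanged, the covariate is no longer matched to the outcome. Baseline cognition is probably a weak predictor of change in HbA1c, grip strength or a blood marker. The measurement that predicts that change best is on file and would be left out of the model.

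For the staged complications, a chi-squared test on a two-by-five table treats the stages as unordered labels and takes no account of the stage at which each patient started. Both pieces of information are collected.

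At stake are wider confidence intervals and lower power for secondary outcomes. Nothing here touches the primary comparison.

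**Working it through.** **The plan's own figure.** Inputs, from the Sample Size section: mean MMSE changes −0.33 (SD 2.58) and −1.45 (SD 3.55), two-sided 5%, power 80%.

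- Difference: 1.45 − 0.33 = 1.12.
- Common SD: √[(2.58² + 3.55²)/2] = 3.10.
- n per arm = 2 × [3.10 × (1.960 + 0.842)/1.12]² = 120.5, so 121 per arm and 242 in total, as stated.
- With dropout: 242/0.85 gives 285 and 242/0.80 gives 303. The planned 300 corresponds to 19.3% dropout.

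None of this depends on the secondary analysis text.

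**Continuous outcomes.** Take a change score with unit variance at each visit. Let r be the correlation between baseline and follow-up, and c the correlation between the baseline composite and the outcome's own baseline. Assume that the composite relates to follow-up only through the own baseline. The documents give neither r nor c; both are assumptions.

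- Residual variance adjusting for own baseline: 1 − r².
- Residual variance adjusting for the composite: 2(1 − r) − c²(1 − r)².
- Ratio of the second to the first: [2 − c²(1 − r)]/(1 + r).

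| r | c = 0 | c = 0.3 | c = 0.7 |
|---|---|---|---|
| 0.5 | 2/1.5 = 1.33 | 1.955/1.5 = 1.30 | 1.755/1.5 = 1.17 |
| 0.7 | 2/1.7 = 1.18 | 1.973/1.7 = 1.16 | 1.853/1.7 = 1.09 |

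With c between 0.3 and 0.7, the excess variance is 9% to 30%. Confidence intervals are then √1.09 = 1.04 to √1.30 = 1.14 times as wide. The column c = 0 is the limit where the composite explains nothing. It is the inverse of the familiar (1 + r)/2, and it overstates the loss for any outcome related to cognition.

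**Single follow-up visit.** With one post-baseline visit, the visit and group-by-visit terms drop out and the MMRM reduces to analysis of covariance (ANCOVA). The model still works; the only open question is which covariate it contains.

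**Staged outcomes.** This was simulated with 121 per arm and 3000 runs. The assumed control distribution over the five stages was 55/20/13/7/5%, with a common odds ratio between arms. The ordinal analysis was a Mann-Whitney test, used as the equivalent of a proportional-odds score test. Neither analysis used baseline stage, so the difference is due to the ordering alone.

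| Odds ratio | Chi-squared, 4 df | Ordinal | Difference in points | Chi-squared, lowest stage vs. rest |
|---|---|---|---|---|
| 1.0 | 4.2% | 4.6% | – | 4.5% |
| 1.5 | 20.1% | 36.5% | 16.4 | 33.5% |
| 1.8 | 40.2% | 62.1% | 21.9 | 61.2% |
| 2.0 | 54.0% | 76.0% | 22.0 | 74.2% |

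The unordered five-stage test loses about 16 to 22 points.

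**The case against.** The strongest reply is that the text is ambiguous, not wrong. The composite is named because it is the own baseline of the outcome being modelled, so using the same analysis elsewhere may well mean using each variable's own baseline. That reading is natural and nothing excludes it. It stands to this extent: one cannot say that the plan discards the own baselines. But the sentence names one covariate and then repeats the model, so both readings are open and the literal one is inferior.

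Second, covariates for each secondary outcome and the form of an ordinal model are often left to an analysis plan, which is not shown here. That excuses silence. It does not cover a stated model that carries the cognitive covariate to every continuous outcome.

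Third, logistic regression is listed before the chi-squared test, and the choice is left open. It could be ordinal and adjusted for baseline. So the text allows the weaker test and does not impose it.

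Fourth, the losses can be smaller than the tables suggest:

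- The 6-month composite already has its own baseline in the model.
- Single-test endpoints are defined as changes, so their baseline enters through the response. The composite also contains the test itself, which raises c.
- Four degrees of freedom is unrealistic for nephropathy. Renal failure is an exclusion criterion, so the two highest stages should be nearly empty at entry.
- If the stages were dichotomised at the lowest one, the simulated loss was only about 1 to 3 points.

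All four qualifications stand. They limit the size of the point without removing it.

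**Conclusion.** The point holds as a matter of precision in secondary outcomes. As worded, the plan leads to the composite as the covariate for all secondary continuous outcomes, and it permits an unadjusted, unordered test for two five-stage outcomes whose baseline stage is known.

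The size is illustrative. Variance is inflated by about 9% to 30%, assuming r of 0.5 to 0.7 and c of 0.3 to 0.7. About 16 to 22 points of power are lost for an unordered five-stage test at odds ratios of 1.5 to 2.0, under the assumed stage distribution. The further effect of adjusting for baseline stage was not quantified. Linear-model variance formulas do not carry over to a proportional-odds model.

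A reader might infer more, but the documents do not support it:

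- **Bias, or a test that mainly reflects baseline differences.** Under randomisation a comparison at follow-up remains valid. The protocol does not say that most patients stay in their baseline stage, nor that follow-up stage alone is what will be compared.
- **A model that cannot be fitted to the CGM and diet measures.** It reduces to ANCOVA.
- **A threat to the main result.** The primary analysis and the 242/300 sample size are untouched.

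**What to change.** Amend the two sentences on secondary outcomes in Data Analyses to say that:

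1. each secondary continuous outcome is analysed with its own baseline value as covariate, in place of the baseline composite, and the model reduces to ANCOVA for the CGM and diet measures with only an 18-month follow-up;
2. retinopathy and nephropathy stages are analysed by proportional-odds regression adjusted for baseline stage, in place of the chi-squared test, with a rule set in advance for collapsing sparse stages.

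The cost is two or three sentences, with no new data and no change to the sample size. The small downside is reliance on the proportional-odds assumption and some loss of detail where stages are collapsed. The adjusted odds ratio is also conditional on baseline stage and should be reported as such.

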#### Adverse Events and Serious Adverse Events

To evaluate the safety of the intervention, all adverse events and serious adverse events will be monitored during this trial. Information to be collected about adverse events will include their date of onset, severity, associated treatment, consequences, and causation. Serious adverse events will be reported to the principal investigator, IRB, and co-researchers immediately.

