##### Physical Exercise and Self-Monitoring of Physical Activity

All participants will engage at least twice a month in a physical exercise program provided at participating institutions by study physiotherapists or trained instructors, which consists of aerobic exercise, muscle strength training, postural balance retraining, and dual-task training, namely “cognicise” (“cogni” for cognition + “cise” for exercise), involving physical and cognitive tasks. The combined activity program intervention including cognicise was shown to improve cognitive and physical performance in older adults with MCI (Shimada et al., 2018). This program will be composed of a 5-min medical check (blood pressure, pulse rate), a 15- to 20-min training including stretching, muscle strength exercise and postural balance training, a 5-min rest, a 20- to 30-min aerobic exercise, a 5-min rest, and a 20- to 30-min dual-task training. The aerobic exercises, including stair stepping and endurance walking will be performed with the mean aerobic exercise intensity set as moderate intensity according to the Karvonen formula: Target heart rate [HR] = [40–60% × (maximum HR – resting HR)] + resting HR. The maximum HR will be estimated for each participant by using the age-predicted maximal HR formula (220 – age). All participants will be assessed for HR immediately after an aerobic exercise based on their pulse rates. The participants will also be recommended to conduct daily home-based muscle-strengthening exercises, walking, and dual-task training at least twice a week, as well as to self-monitor these activities using study-provided booklets and pedometers.

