#### Control Group

Participants in the control group will receive usual care and treatment for T2DM based on the Treatment Guidelines for Elderly Patients with Diabetes Mellitus 2017 as in the intervention group. Additionally, at baseline, they will receive general instructions on prevention of dementia including the benefits of physical activities, healthy diet, cognitive activities, and social participation.

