#### Data Collection Forms and Data Monitoring

All measurements will be assessed by trained personnel. Most outcome measurements will be collected using papers forms at each institution. Then, these data will be collected through entry of these data by assessors using electronic data capture (EDC) systems. Paper forms will be retained as back-ups at each institution as required.

On-site monitoring will be conducted at each institution to ensure that the patient rights are protected, the reported data are accurate, and the conduct of the trial is compliant with the current approved protocol. The monitor will ensure that (1) written informed consent is obtained from all participants before their participation in this trial; (2) primary outcome data reported in the EDC are complete and accurate; and (3) all adverse events and serious adverse events are reported appropriately.

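### The between-arm test of all recorded non-serious adverse events is exposed to unequal detection, because only the intervention arm has frequent supervised sessions with unblinded staff

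*Protocol article*

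**What the plan says.** The section Adverse Events and Serious Adverse Events states that "all adverse events and serious adverse events will be monitored during this trial". It lists what is recorded for an event (onset, severity, treatment, consequences, causation), but not how or at which contacts events are elicited. Under Data Collection Forms and Data Monitoring, the monitor checks that "all adverse events and serious adverse events are reported appropriately".

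Data Analyses then states: "Frequencies of adverse events and serious adverse events will be summarized and compared between the intervention and control groups", with the chi-squared or Fisher's exact test, and P-"values <0.05 will be considered statistically significant".

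The arms differ in contact:

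- **Intervention arm.** "All participants will engage at least twice a month in a physical exercise program provided at participating institutions by study physiotherapists or trained instructors". This sentence stands under the Intervention Arm heading, so it refers to that arm only. Each session opens with a short check of blood pressure and pulse, and a group meeting follows it (Social Participation).
- **Control arm.** "Participants in the control group will receive usual care and treatment for T2DM", plus general advice once at baseline.
- **Both arms.** Outcome assessments take place at baseline, 6 and 18 months.

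Continuous glucose monitoring (CGM) is done in both arms, but clinicians do not see the control arm's results (Management of Metabolic and Vascular Risk Factors). Blinding is stated for staff who collect the primary outcome, not for those who record adverse events (Randomization and Blinding).

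**The concern.** The number of non-serious events on record depends on how often events occur and on how often someone from the study is there to hear of them. Here the second factor differs by design. A muscle complaint, a minor illness or a dizzy spell can be mentioned to staff within about two weeks in one arm. In the other it may have to wait for a routine appointment or the next assessment. The staff who hear of it know the allocation.

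Nothing in the safety, monitoring or analysis text limits the comparison to contacts that both arms have. A significance test on these counts then reflects detection as well as risk. At stake is a false signal of harm against the programme, or a true reduction in minor events that goes unseen.

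**Working it through.** **1. Contact count.** The article gives no figure for this, so there is none to reproduce. Inputs are at least 2 sessions per month and an 18-month trial: 2 × 18 = 36 sessions, provided they run throughout and are attended. Dietician counselling takes place at medical examinations about every two months (18 / 2 = 9), so it need not add visits. If controls have the same examinations, those contacts are shared. The clear excess is the 36 exercise sessions, each followed by a meeting.

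**2. Does the text limit which events enter the test?** Set side by side, the adverse-event section covers all events, the monitoring section checks that they are reported, and the analysis section compares their frequencies. None mentions a common set of questions or visits. Monitoring can confirm that a known event was reported. It cannot make up for an event nobody heard of.

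**3. What unequal detection would do.** The detection rates and true risks below are assumptions; the article gives none.

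The true risk p is the same in both arms, with n = 150 per arm (300 / 2). The recorded proportions are p1 = p × d1 (intervention) and p2 = p × d2 (control), where d is the share of affected patients detected. With p̄ = (p1 + p2)/2, the two-sided 5% test rejects when the observed difference exceeds c = 1.96 × √[2p̄(1 − p̄)/n]. The rejection probability is Φ[(p1 − p2 − c)/s] plus a negligible opposite tail, where s = √[p1(1 − p1)/n + p2(1 − p2)/n].

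Worked case: p = 30%, d1 = 90%, d2 = 70%. Then p1 = 0.27, p2 = 0.21 and p̄ = 0.24, so c = 1.96 × 0.0493 = 0.0967 and s = 0.0492. Φ[(0.06 − 0.0967)/0.0492] = Φ(−0.75) ≈ 0.23.

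| True risk, both arms | Detection, intervention v control | Recorded | Chance of a false significant difference |
|---|---|---|---|
| 30% | equal | equal | 5% |
| 30% | 90% v 80% | 27% v 24% | 9% |
| 30% | 90% v 70% | 27% v 21% | 23% |
| 30% | 90% v 60% | 27% v 18% | 46% |
| 50% | 90% v 70% | 45% v 35% | about 42% |
| 50% | 90% v 60% | 45% v 30% | 77% |
| 5% | 90% v 70% | 4.5% v 3.5% | 7% |

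Exact binomial enumeration gives the same values to within about one percentage point. The problem grows with how common the event is and with the detection gap. For rare events or a small gap it is slight.

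**4. A remedy that fails.** Suppose events first noted at exercise or counselling sessions were left out of the test. Only one arm would lose events. With 30% true risk, full detection in both arms, and half of the intervention arm's events first mentioned at a session (all assumed), the test would compare 15% with 30% and declare a false benefit in about 88% of trials.

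**The case against.** The strongest reply is that the mechanism is inferred. The article does not say where adverse events are elicited. The session check covers blood pressure and pulse only. The diaries record exercise, weight, meals and social activity, not adverse events. An elicitation schedule may stand in the full protocol or in the timeline figure, which is not shown. All of this is right. A reader might infer that the comparison is biased by a known amount; the article supports only that it is open to bias.

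A reader might also infer that this is the trial's sole safety comparison, so that a true fall in hypoglycaemia or falls would be lost. The documents contradict that. Hypoglycaemia questions and CGM time below 70 mg/dL are planned for participants in both arms. Falls in the past 12 months are asked of all participants within the geriatric assessment at baseline, 6 and 18 months. Those two outcomes already have common questions.

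Three further points stand. Serious events tend to surface without study visits. The choice of test is not at fault, since any test on unequally detected counts has the same weakness. The likely direction overstates harm from the intervention rather than hiding it.

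What remains is that the article does fix a tested comparison of all events alongside a one-sided contact schedule. A schedule elsewhere would help only if it based the test on contacts that both arms share. Overstating harm is still an error in the safety conclusion.

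**Conclusion.** The point holds in limited form. As written, the comparison of non-serious adverse events is exposed to differential detection, most likely inflating apparent events in the intervention arm. Its size cannot be computed from the article. Under the assumptions tabulated, the false-positive rate runs from the nominal 5% with equal detection to 77% with a wide gap and common events. It stays below 10% for rare events or a modest gap.

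This rests on sessions running for the whole 18 months and on events mentioned there being recorded, which follows from the commitment to monitor all events but is not spelled out. The primary cognitive analysis is unaffected.

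**What to change.** Amend the adverse-event section and Data Analyses as follows:

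1. Make the main between-arm comparison of non-serious events the events elicited in both arms with the same fixed questions at shared contacts, at least the 6- and 18-month visits. The questions should cover the whole interval since the previous shared visit. Count an event there whether or not it was already mentioned at an exercise or counselling session, so that neither arm loses events.
2. Compare serious adverse events in full.
3. Record the contact at which each event was first noted.
4. Present all recorded events, including injuries during sessions, as a descriptive summary by arm with a note on unequal contact.

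The cost is a short question set at existing visits, one field on the adverse-event form and a few sentences of text. The downside is that some mild events may be missed through recall, since the second interval is 12 months and participants are cognitively impaired. The study partner required at inclusion could answer alongside the participant. Missed events that were recorded elsewhere remain in the descriptive summary.
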